### 3 ANALYSIS – GENERAL CONSIDERATIONS

#### 3.1 DESCRIPTIVE STATISTICS

Clinical and demographic variables measured at baseline will be summarised both overall and by trial arm to assess the comparability of the randomised treatment groups. Baseline comparisons will be descriptive only and no formal significance testing will be carried out on baseline variables. Binary or categorical variables will be summarised using sample size (n), number of missing observations (n missing) and proportions within each group. Continuous variables that are approximately normally distributed will be summarised by n, n missing, mean and standard deviation. Continuous variables that are not normally distributed will be summarised using n, n missing, median, minimum and maximum.

Visit windows will be summarised graphically by creating a histogram using the days from baseline to each visit including lines denoting the window for each visit.

#### 3.2 CHARACTERISTICS OF PARTICIPANTS

The patient population at baseline will be reported by treatment group and overall and characterised in terms of:

- Age (computed from age at base line visit: VISDAT-BRTHDAT)
- The number of participants in each of the age groups according to EudraCT guidelines will be reported. These age groups are (adults (18-64 years), from 65-84 years, 85 years and over). Additionally we will report numbers by additional age groups: 18-54 years, 55-64 years, 65-74 years, 75 to 84 years and 85 years and over.
- Gender (SEX)
- Ethnicity (ETHNIC)
- Past medical history (including type II diabetes and coronary artery disease). Presence of: hypertension (HYPYN), diabetes (DIAYN), if no diabetes impaired fasting glucose and/or impaired glucose tolerance (IMGYN), Ischaemic heart disease (IHDYN), heart failure (HFYN), Atrial fibrillation (AFYN), Cerebrovascular disease (CVDYN), peripheral vascular disease (PVDYN), renal disease (RENYN), childhood urinary tract infection (CUTIYN), adulthood urinary tract infection (AUTIYN), Thyroid disease (THYYN), Anaemia (ANAYN), Osteopenia (OPEYN) and Osteoporosis (OPOYN).
- Current medication (CMTRT)
- Smoking status (SMOKSTAT), categorised as never smoker, current smoker or former smoker.
- Weight (WEIGHT)
- Height (HEIGHT)
- Waist circumference (WSTCIR)
- Hip circumference (HIPCIR)

- Office measurement of diastolic BP right arm (DIABPR)
- Office measurement of systolic BP right arm (SYSBPR)
- Office measurement of diastolic BP left arm (DIABPL)
- Office measurement of systolic BP left arm (SYSBPL)

Laboratory and ECG (normal/abnormal(NCS)/abnormal(CS)) test results

- ACR (ALBCREAT)
- eGFR (GFR)
- Potassium (K)
- Creatinine (CREAT)
- Electrocardiogram (ECGCLSIG), categorised as normal, abnormal but not clinically significant or abnormal and clinically significant.

The following test results are recorded on the baseline CRF (text field) and also in the additional laboratory test results. In the analysis the additional laboratory test result CRF will be used to populate the data.

- BNP (BNP) recorded using pg/mL. Where BNP is recorded as ng/L or pmol/L this will be converted to pg/mL.
- HbA1c (IFCC) [HBA1C] [HBA1C]. HBA1C can be recorded using mmol/mol and mmol/molHb. Units will be reported as mmol/mol. Where both IFCC and DCCT measures are recorded, the IFCC will be solely reported. Where only DCCT has been collected it will be converted to IFCC. IFCC can be calculated from DCCT using the following formula:  $IFCC = (DCCT - 2.15) \times 10.929$ .
- Lipid profile (serum total cholesterol, serum HDL cholesterol, serum LDL cholesterol, triglyceride and cholesterol to HDL cholesterol ration measurement) (CHOL, HDL, LDL, TRIG and CHOLHDL)
- Practice ID (from Sortition) will be presented by randomised group and overall.

The following test results are recorded on the baseline CRF (coded as normal/abnormal but not clinically significant/abnormal and clinically significant. Where an abnormal result is recorded the actual value should be recorded as a free text field. The values recorded in the free text will be presented using summary statistics, either mean and standard deviations or median and interquartile range as appropriate.

- Full blood count (FBCCLSIG).
- Liver Function Tests (LIVCLSIG)
- Bone Profile Tests (BONCLSIG)
- Fasting Blood sugar (FBSCLSIG)

### 3.3 FLOW OF PARTICIPANTS THROUGH THE TRIAL

Recruitment, randomisation and follow-up of participants will be summarised using a CONSORT flow-diagram. An example is shown in Appendix IV. Reasons for all post randomisation discontinuations will be included.

### 3.4 DEFINITION OF POPULATION FOR ANALYSIS

The primary analysis will be carried out on all randomised participants, on an Intention to treat (ITT) basis, assuming non-informative censoring for those withdrawn or lost to follow-up. Based in the ITT principle, participants who are withdrawn from treatment (e.g. for safety reasons) but consent to continue follow-up will be included in the ITT analysis. Participants who are withdrawn or lost to follow-up will be censored at the date of withdrawal or date of last follow-up, respectively. All participants will be analysed in the groups to which they were allocated, regardless of treatment compliance.

The safety population will include all participants who took at least one tablet of the study medication. The diary card records the response to the question: "Please confirm you are taking the spironolactone as prescribed?". If the participant records they are taking the medication at the first post-randomisation visit (week 12) they will be included in the safety population. If they record they are not taking the medication, the study discontinuation form will be reviewed to determine whether they took at least one dose. If there is no information available on use of medication it will be assumed they took at least one dose.

### 3.5 POOLING OF INVESTIGATIONAL SITES

Data will be collected across all GP practices that randomised patients in the study. These data will be analysed together and GP practice will be included as a random effect in the statistical analysis.

### 3.6 DATA MONITORING COMMITTEE

The trial will have a Data Monitoring and Ethics Committee (DMEC), who will report to and advise the Trial Steering Committee (TSC) who, in turn, will report to and advise the Trial Management group. Both the DMEC and TSC will have independent chairs and 'stop rule' authority to advise early termination of the trial in the event of safety concerns or futility wither through poor recruitment, lack of events, or lack of any treatment effect ('stop rules' to be defined by DMEC). All committees will convene regularly prior to, during, and following the trial. Together, the responsibilities of the committees are to: (a) safeguard the safety, rights and well-being of the trial participants; (b) systematically monitor the trial data and review any analysis as outlined in the Statistical Analysis Plan or as requested by the TSC; (c) make recommendations to the TSC as to whether the trial is operating as expected or if there are any ethical or safety reasons why the trial should not continue; (d) consider data emerging from other related studies and its potential impact on the trial, if requested by the TSC; (e) pick up any trends, such as increases in un/expected events, and take appropriate action; (f) seek additional advice or information from investigators where required; and (g) act or advise, through the Chairman or other consultant, on incidents occurring between meetings that require rapid assessment.

## 4 PRIMARY ANALYSIS

### 4.1 PRIMARY OUTCOME

The primary analyses will be conducted on all randomised participants, applying the principle of intention-to-treat (ITT), as far as is practically possible, given any missing data. Specifically, the participants will be analysed in the groups to which they were allocated regardless of compliance with the allocated treatment. The primary outcome will be analysed using a mixed effect Cox proportional-hazards method, with a fixed effect for randomised group and practice included as a random effect, with unstructured variance covariance matrix. Results will be presented as a hazard ratio with 95% confidence interval and associated two-sided P-value. A p-value of 0.05 will be used to assess statistical significance. Time to event will be summarised by randomised group using medians and interquartile range.

TABLE 1 DUMMY TABLE FOR PRIMARY OUTCOME

|                    | TREATMENT      |                                  |                  | CONTROL        |                                  |                  | MODEL ESTIMATES |                   |                   |             |
|--------------------|----------------|----------------------------------|------------------|----------------|----------------------------------|------------------|-----------------|-------------------|-------------------|-------------|
|                    | (N=)           |                                  |                  | (N=)           |                                  |                  |                 |                   |                   |             |
|                    | AVAILABLE
N | NUMBER REACHED
ENDPOINT, N(%) | TIME TO
EVENT | AVAILABLE
N | NUMBER REACHED
ENDPOINT, N(%) | TIME TO
EVENT | HAZARD
RATIO | 95%
LOWER C.I. | 95%
UPPER C.I. | P-
VALUE |
| Primary
outcome |                |                                  | Median
(IQR)  |                |                                  | Median
(IQ)   |                 |                   |                   |             |

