## 12.3. Sample Size Determination

A UK representative spread of practices will be achieved by stratifying practice postcode location into quartiles of Townsend Deprivation Score and selecting practices that agree to take part sequentially until each deprivation quartile practice target is reached. This strategy will most probably ensure that populations selected will also be representative for ethnicity but the sequential practice selection strategy will be examined after ten practices have been selected for each deprivation quartile to ensure practices serving high proportions of ethnic minorities are included in the final five places, if this has not already occurred in the earlier selections.

The estimate for the cardiovascular (CV) event rate (defined by hospitalisation for coronary heart disease, heart failure, ischemic stroke and peripheral arterial disease) and total mortality rate in patients with CKD 3b (eGFR 30-44 ml/min/1.73m^2) being 11.29 and 4.76 per 100 person years respectively gives a combined

event rate of 16.05 per 100 person years [5]. In those with eGFR in the range 45-50 ml/min/1.73m^2, the event rate is conservatively estimated to be 0.667 times as high (10.7 events per 100 person years[76] and we assume half the participants will fall in this range giving an overall event rate of 13.4 events per 100 person years. To detect a 20% relative risk reduction in death or cardiovascular events within 3 years in the intervention group as compared with the control group (i.e. hazard ratio=0.8) with an anticipated treatment withdrawal rate of 13% (which gives a diluted estimated treatment effect = 0.84) and a two sided significance of 0.05, 1511 participants per group (3022 total) are required at 80% power and assuming 10% attrition rate.

We have decided to power the trial conservatively on a 20% risk reduction since this proposed treatment effect is around half the risk reduction observed in the ARA mild heart failure trial (EMPHASIS). The estimated hazard ratio in the EMPHASIS eplerenone versus placebo mild heart failure trial (only mildly symptomatic patients were included) were 0.63 (CI 0.54-0.74, p<0.001) for the composite endpoint of death from CV causes or hospitalisation for heart failure at the median follow up of 21 months. The conservative upper CI for the treatment effect was 26% reduction. The placebo CV event rate in EMPHASIS trial was similar to observational data on CV events in CKD 3b patients [5].

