#### **12.7. The Level of Statistical Significance**

5% significance level (2-sided)

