## 6 SENSITIVITY ANALYSIS

### 6.1 COVARIATE ADJUSTMENT

To test the robustness of the result for the primary outcome, a sensitivity analysis will be carried out, using the cox proportional hazards model, adjusting the following pre-specified baseline prognostic factors: diastolic (DIABPR/DIABPL) and/or systolic blood pressure (SYSBPR/SYSBPL) above or below NICE target, type II diabetes (DIAYN) and coronary artery disease (IHDYN) BP targets will be based on the following measures of clinical blood pressure:

- People aged under 80 years: lower than 140/90 mm Hg (systolic/diastolic)
- People aged 80 years or over: lower than 150/90 mm Hg (systolic/diastolic)

As blood pressure is recorded in both arms at each visit, we will consider the average of the two measures as meeting the criteria.

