**TABLE 4 DUMMY TABLE FOR THE ANALYSIS OF THE PRIMARY OUTCOME**

| HAZARD RATIO  | 95% LOWER C.I. | 95% UPPER C.I. | P-VALUE |
|---------------------------|----------------|----------------|---------|
|                           |                |                |         |

1. Adjusted for the following covariates: systolic or diastolic blood pressure above NICE target, type II diabetes, coronary artery disease and GP practice.

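### The primary Cox model adjusts for practice alone; age, sex, smoking and prior AF, cerebrovascular or peripheral vascular disease enter no primary-outcome model, which forgoes some power (size undocumented) but leaves the test valid

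*Combined protocol and SAP*

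**What the plan says.** SAP 4.1 specifies a mixed effects Cox model "with a fixed effect for randomised group and practice included as a random effect". No patient-level covariate is included. Protocol 12.2 says the same: a survival model adjusted for practice.

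One adjusted sensitivity analysis is planned, in SAP 6.1. The footnote to its dummy table (SAP Table 4) reads "Adjusted for the following covariates: systolic or diastolic blood pressure above NICE target, type II diabetes, coronary artery disease and GP practice". Blood pressure enters there as a yes/no flag, from the average of the two arm readings. The systolic limit is 140 mm Hg below age 80 and 150 mm Hg from age 80. The subgroup models in SAP 7 reuse the same three factors.

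SAP 3.2 lists age, sex, smoking status, atrial fibrillation (AFYN), cerebrovascular disease (CVDYN) and peripheral vascular disease (PVDYN) among the baseline data, for description only. SAP 4.4 expects baseline covariates to be complete. Its rule for adding baseline predictors of dropout is written for the secondary outcomes and does not reach the primary model.

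**The concern.** In a Cox model, leaving out baseline factors that predict the outcome moves the estimated hazard ratio toward 1 relative to the covariate-conditional one, and the test loses power. Covariates already collected can recover that power without further recruitment.

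Three features of this plan make the omission worth attention.

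- The endpoint counts first onset of conditions absent at baseline. Prior atrial fibrillation, cerebrovascular or peripheral vascular disease therefore affects which events a participant can still contribute, but only coronary disease reaches SAP 6.1.
- Randomisation is stratified by practice alone (SAP 2.5), so nothing in the design balances age, and the 6.1 robustness check cannot correct for a chance age difference.
- The limit for the blood pressure flag changes at age 80, so without age in the model the flag mixes pressure with age. This touches the 6.1 model and the blood pressure subgroup. It does not touch the primary test, which contains no blood pressure term.

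**Working it through.** **1. Terms in each primary-outcome model**

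| Model | Terms |
|---|---|
| Primary (SAP 4.1, protocol 12.2) | group, practice |
| Sensitivity (SAP 6.1, Table 4) | group, practice, BP flag, type II diabetes, coronary disease |
| Subgroup (SAP 7) | group, practice, one of those three factors, its interaction with group |

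Age appears only as the switch between blood pressure limits. A reading of 145/85 is above target at 79 and below target at 80.

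**2. The plan's own sample size**

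Inputs are from protocol 12.3 and 12.7: two-sided 5%, 80% power, hazard ratio 0.8 with 13% treatment withdrawal, 3 years, "giving an overall event rate of 13.4 events per 100 person years", and "1511 participants per group (3022 total) are required at 80% power and assuming 10% attrition rate".

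- Dilution on the log scale: HR = 0.8^0.87 = 0.8235.
- Events (Schoenfeld): 4(1.960 + 0.842)² / (ln 0.8235)² = about 833.
- Three-year event probabilities: control 1 − exp(−0.134 × 3) = 0.331; treated 1 − exp(−0.134 × 0.8235 × 3) = 0.282; mean 0.3064.
- Per group: 833 / 0.3064 / 2 / 0.9 = 1511.

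The stated size reproduces. It does so with 0.8235 and not with the printed diluted value of 0.84, which would need 1859 per group. The steps below use 0.8235.

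**3. Gain from adjustment**

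The documents give no hazard ratio for any covariate. The assumed quantity is s, the SD of the covariates' combined log hazard, taken from 0.3 to 1.0. For scale, age alone with an assumed SD of 9 years gives s = 0.9 × ln(1.65) = 0.45 if its hazard ratio is 1.65 per decade, and 0.9 × ln(2.23) = 0.72 if it is 2.23.

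Trials were simulated with 1500 runs per row. The unadjusted hazard ratio was fixed at 0.8235, so the plan's effect is read as unadjusted. The planned size after loss is 3022 × 0.9 = about 2720, with about 833 events. Power is the normal approximation to the mean z. The equivalent gain in patients is (ratio of mean z)² − 1.

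| s (assumed) | Conditional HR | Power, unadjusted | Power, adjusted | Equivalent extra patients |
|---|---|---|---|---|
| 0.3 | 0.821 | 80.6% | 81.7% | 3% |
| 0.5 | 0.816 | 80.6% | 83.9% | 9% |
| 0.7 | 0.809 | 78.2% | 85.2% | 20% |
| 1.0 | 0.793 | 78.8% | 91.5% | 46% |

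The true unadjusted power is 80% in every row; the spread around it is simulation error. Practice was not simulated.

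The supplementary tables show 1372 randomised, with 94 + 96 = 190 events in the analysis excluding peripheral arterial disease. At that scale (about 188 simulated events) power moves from 25.5% to 25.8% at s = 0.3 and from 26.4% to 30.3% at s = 1.0.

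**4. Chance imbalance in age**

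With the assumed SD of 9 years, the standard error of the between-group difference in mean age is 9 × √(2/1511) = 0.33 years. One such standard error shifts the log hazard ratio by 0.33 × ln(1.65)/10 = 0.016, or by 0.33 × ln(2.23)/10 = 0.026. The standard error of the log hazard ratio itself is about 2/√833 = 0.069.

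**The case against.** The plan is coherent as it stands. Protocol 12.2 names the primary model and the three sensitivity factors in advance, SAP 4.1 and 6.1 follow it, and the only stratification factor is in the model. The marginal hazard ratio is a legitimate estimand. The protocol's background (section 5, on CKD and cardiovascular risk) says conventional risk factors predict less well in CKD than in the general population, and much less well than eGFR and protein excretion. Prior disease also removes the first-onset route for that condition, so its net effect on the composite is uncertain. All of this stands. It limits the size of the gain and does not show that the gain is nil.

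Four stronger readings are tempting, and the documents do not support them.

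- *The primary result is biased.* It is not. The unadjusted hazard ratio differs from the conditional one by non-collapsibility, and the test keeps its level.
- *The trial has only 72% to 76% power.* Simulations that treat 0.826 (linear dilution, 1 − 0.87 × 0.2) as the conditional effect give such figures for age hazard ratios of 2.23 and 1.65 per decade. The protocol does not call its effect conditional, and its sample size reproduces at 80% with an unadjusted effect.
- *Adjustment is worth a firm 15% to 22% more events.* That depends on assumed covariate effects and leaves out the low end of the range.
- *Age is absent from every efficacy model.* The SAP 4.4 dropout rule could bring it into the secondary-outcome models.

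An age imbalance would also not go unseen, because baseline characteristics are reported by group. At the planned size it would usually be small against the standard error of the treatment effect.

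**Conclusion.** The omission is certain from the documents. Six baseline variables that are collected and expected complete enter no primary-outcome model, and the 6.1 flag is entangled with age. The consequence is lost efficiency only.

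The direction of the power gain is secure if the covariates are prognostic; its size is not documented. At the planned size it is about 1 to 13 points for s from 0.3 to 1.0, and about 3 to 7 points for s from 0.5 to 0.7. At 1372 participants with about 190 events it is about 0.3 to 4 points. Given the protocol's own ranking of predictors, the named factors alone may deliver the low end. Baseline eGFR and ACR, also collected and also absent from these models, are stronger candidates on that ranking. This is an inexpensive improvement to a valid analysis.

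**What to change.** Before any unblinded analysis, prespecify in SAP 4.1 fixed effects for age (continuous), sex, smoking status, systolic blood pressure (continuous, mean of the left and right readings), DIAYN, IHDYN, AFYN, CVDYN and PVDYN. Consider adding baseline eGFR and ACR. State that the primary hazard ratio is conditional on these covariates, and keep the group-plus-practice model as the sensitivity analysis. Change protocol 12.2 to match and record the change in SAP section 11.

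At minimum, leave the primary model alone, add these covariates to SAP 6.1, and replace the yes/no pressure flag there with continuous systolic pressure plus age.

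No new data are needed. The costs are a protocol and SAP change, a conditional rather than marginal hazard ratio under the full option, and a few missing baseline values to handle under SAP 4.4. Timing matters because SAP 2.5 leaves the trial statisticians unblinded. If outcomes by group have already been seen, the adjusted model can be reported only as post hoc. SAP 4.6 makes practice a fixed effect where 4.1 makes it random; the same edit should reconcile them, although this point does not depend on which is kept.

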#### 4.1.1 DEFINITION OF THE PRIMARY OUTCOME

If an event (as defined in section 2.2.1) occurs the primary outcome will be defined as time from randomisation (RANDDAT) to time of any of the following: time of first onset of or hospitalisation (HOSPDAT), time of first onset of cardiovascular disease (CVDSTDAT), or time of death (DEATHDATE). If multiple events occur then the primary outcome will be defined using the earliest occurring event. In addition, the adjudication by the endpoint committee will be used to determine if the event constitutes an endpoint as defined in the protocol (DECISION).

For those participants not experiencing a relevant event by the end of the study the primary outcome will be calculated as time from randomisation (RANDDAT) to censoring: either date of withdrawal if the participant has withdrawn completely from the study and further follow-up (LVISDAT) or date of last follow-up (VISDAT) if continuing follow-up. For participants who are withdrawn from treatment but consent to further follow-up, censoring will be based on date of last follow-up rather than date of withdrawal based on the ITT principle. Some participants may have multiple withdrawal dates, for example if a participant was withdrawn from medication for safety reasons but consented to further follow-up and then withdrew consent for follow-up at a later date. In these cases the date of final follow-up should be used as the date of censoring. A binary variable will code whether an event as defined in section 2.2.1 has occurred or the participant has been censored.

Two variables will be derived, PEVENT = 1, if the participant experiences a primary outcome event and 0 otherwise, DATEPEVENT = first occurring date of primary outcome event. Derived from:

PEVENT=1 if {{HOSPYN=Yes OR FSONSETCVDYN=Yes OR DEATHYN=Yes} AND {DECISION=Yes}}

PEVENT=0 if {HOSPYN=No AND FSONSETCVD=No AND DEATHYN=No} OR {ANY OF HOSPYN, FSONSETCVD, DEATHYN =Missing AND ALL NON MISSING HOSPYN, FSONSETCVD, DEATHYN =No} OR { ANY OF HOSPYN, FSONSETCVD, DEATHYN =Yes AND DECISION=No AND ALL NON MISSING HOSPYN, FSONSETCVD, DEATHYN =No}

IF PEVENT=1 THEN DATEPEVENT=Date first occurrence of ANY of HOSPYN, FSONSETCVD, DEATHYN, HDYN, STROKEYN, PADYN, HFYN

IF PEVENT=0 THEN DATEPEVENT={Date of last follow up OR date of last contact OR date of withdrawal IF FOLLOWUP=2}

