### 2.2.2 PRIMARY LONG-TERM OUTCOMES

Annual rates collected via medical notes review of death, hospitalisation for heart disease (coronary heart disease, arrhythmia, atrial fibrillation, sudden death, resuscitated sudden death), stroke, transient ischaemic attack, peripheral arterial disease or heart failure. First onset of any condition listed above not present at baseline.

The following variables will be used to record the occurrence of an event HOSPYN (hospitalised), FSONSETCVD (first onset of cardiovascular disease) and DEATHYN (death). In addition the endpoint will be adjudicated by the endpoint committee (DECISION). If the event is not judged to be an endpoint according to the protocol OR it is not the first onset of hospitalisation for CVD, or death OR there is insufficient information to determine it is an endpoint according to the protocol OR the endpoint committee determines it does not constitute as an endpoint for any other reason then the external adjudication will be coded "No". The reason that the event does not meet the endpoint condition will be captured in the variables REASONIFNO and OTHREASONIFNO. If any of the previously mentioned variables are coded "Yes" and DECISION is coded "Yes" then a primary outcome event will be recorded as having occurred.

If more than one primary outcome event has occurred, time to event will be computed using the date of the earliest occurring event minus RANDDAT (date of randomisation).

If a participant does not experience a primary outcome event they will be censored either at the date of last follow-up, the date of last contact or at the date of withdrawal from the study. Based on the intention to treat (ITT) principle, participants who withdraw from treatment but consent to further follow-up will be censored at the date of last contact rather than the date of withdrawal from treatment.

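### The SAP's derivation code for the primary endpoint contradicts its own prose on status and date, and code and prose alike count a death only if the endpoint committee accepts it

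*Combined protocol and SAP*

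**What the plan says.** SAP 4.1.1 first states the rule in prose. Status has two values: "A binary variable will code whether an event as defined in section 2.2.1 has occurred or the participant has been censored". The sentence that introduces the code says "PEVENT = 1, if the participant experiences a primary outcome event and 0 otherwise, DATEPEVENT = first occurring date of primary outcome event" and then presents the code as the derivation.

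The code has three parts that matter here:

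- **Event:** "PEVENT=1 if {{HOSPYN=Yes OR FSONSETCVDYN=Yes OR DEATHYN=Yes} AND {DECISION=Yes".
- **Non-event, clause for rejected reports:** "ANY OF HOSPYN, FSONSETCVD, DEATHYN =Yes AND DECISION=No AND ALL NON MISSING HOSPYN, FSONSETCVD, DEATHYN =No".
- **Date of an event:** "IF PEVENT=1 THEN DATEPEVENT=Date first occurrence of ANY of HOSPYN, FSONSETCVD, DEATHYN, HDYN, STROKEYN, PADYN, HFYN".

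SAP 2.2.2 is headed as long-term outcomes but describes the same derivation. If a flag and the committee's DECISION are both Yes, "then a primary outcome event will be recorded as having occurred". On dating it says "If more than one primary outcome event has occurred, time to event will be computed using the date of the earliest occurring event". DECISION is coded No on several grounds, among them that "there is insufficient information to determine it is an endpoint according to the protocol", plus a catch-all for any further reason. Death is not exempted.

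The protocol (section 6, and the design summary in 7.1) and SAP 2.2.1 list death from any cause as a component in its own right. They also have a blinded independent committee adjudicate the primary endpoints.

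**The concern.** The primary hazard ratio depends on one status and one date per participant. Here two sets of instructions for both stand side by side and disagree.

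A programmer who follows the code has no status, and so no censoring date, for a participant whose only reported event was rejected. If such participants are left out, an intention-to-treat analysis loses people who were event-free. The same programmer could give an accepted event the date of an earlier report that the committee turned down. A death with DECISION=No is not counted under either set of instructions.

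The trial is open label, so the rate at which suspected events are reported, and hence rejected, can differ by arm. SAP 2 and 2.5 say that the statisticians are not blinded. Any choice between code and prose would therefore be made by people who can see allocation.

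**Working it through.** This is a point of derivation logic. The plan states no figure that depends on it, so there is none to reproduce.

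**1. Status.** Each of the three flags can be Yes, No or missing, and so can DECISION: 3 × 3 × 3 × 3 = 81 states.

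- Flag patterns with no Yes: 2 × 2 × 2 = 8. With at least one Yes: 27 − 8 = 19.
- PEVENT=1 needs a Yes flag and DECISION=Yes: 19 states.
- The first two PEVENT=0 clauses cover the patterns with no Yes: 8 × 3 = 24 states.
- The third PEVENT=0 clause needs a flag that is Yes while every non-missing flag is No. A Yes flag is non-missing, so this holds in 0 of 81 states.
- No status: 81 − 19 − 24 = 38, of which 19 have a reported event with DECISION=No and 19 have one with DECISION missing.

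If the clause is read as meaning all *other* non-missing flags, it covers the patterns with exactly one Yes: 3 × 2 × 2 = 12. Then 19 − 12 = 7 rejected states and the 19 missing-decision states remain, so 26 are still undefined. Under the prose rule all 38 become 0, giving 19 event and 62 non-event states. These are logical states; 38 of 81 is not a share of participants.

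**2. Date.** Suppose a hospitalisation report at month 6 is rejected and a stroke at month 20 is accepted. At participant level PEVENT=1, and the coded date is month 6. The introductory prose and SAP 2.2.2 give month 20.

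**3. Deaths.** The code and SAP 2.2.2 agree that DECISION=Yes is required. With DECISION=No, the prose rule gives PEVENT=0, so a death is treated as a censored observation although death is a component.

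**4. Illustrative size.** From SAP 2.4: control rate 13.4 per 100 person-years, hazard ratio 0.8, 3 years. A true ratio of 1.00 was also run. Assumptions not in the documents: 30% of true events are deaths; 0% or 5% of deaths are rejected; reports destined for rejection arise at a yearly hazard of r/(1−r) × 0.134, with r between 5% and 30%; participants without status are dropped; accepted events take the date of the first report; there is no practice effect. Each scenario used 400,000 simulated participants.

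Check of the dropped share at a true ratio of 1.00 with no deaths rejected, where h is the hazard of rejected reports: exp(−0.134 × 3) × [1 − exp(−3h)].

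- r = 15%: h = 0.0236; 0.669 × 0.069 = 0.046 (simulated 0.046).
- r = 25%: h = 0.0447; 0.669 × 0.125 = 0.084.
- 15% in one arm and 25% in the other: (0.046 + 0.084)/2 = 0.065 (simulated 0.065).

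| r, control / spironolactone | Deaths rejected | Reference HR | HR, code | HR, prose | Dropped | Accepted events misdated |
|---|---|---|---|---|---|---|
| 15% / 15% | 0% | 1.000 | 0.999 | 1.000 | 4.6% | 3.2% |
| 30% / 30% | 0% | 0.799 | 0.802 | 0.799 | 10.9% | 7.6% |
| 30% / 30% | 5% | 0.809 | 0.815 | 0.811 | 11.5% | 7.7% |
| 15% / 25% | 0% | 0.998 | 1.053 | 0.998 | 6.5% | 4.5% |
| 25% / 15% | 0% | 1.003 | 0.951 | 1.003 | 6.5% | 4.5% |
| 15% / 25% | 0% | 0.804 | 0.852 | 0.804 | 6.8% | 4.5% |
| 25% / 15% | 0% | 0.798 | 0.758 | 0.798 | 6.7% | 4.7% |

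The third row is the largest shift found with equal rejection: 0.815 − 0.809 = 0.006. In the unequal rows the shifts are +0.055, −0.052, +0.048 and −0.040. The prose rule stayed within 0.002 of the reference in every scenario. Rejecting 5% of deaths when 30% of events are deaths loses 0.05 × 0.30 = 1.5% of events. Equally split between arms, that hardly affects the ratio.

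**The case against.** The best defence is that the prose is right and governs. It gives 0 to everyone without a primary outcome event and allows only event or censored. It dates from the primary outcome event, which SAP 2.2.2 ties to an accepted decision. SAP 3.4, 4.1 and 4.4 put all randomised participants in the analysis. If flags and DECISION are held per event record, the date line already refers to accepted records; the endpoint form is not in the documents, so this cannot be excluded. Validation of the primary analysis is planned (SAP 9). For status and date this stands as evidence of intent. It does not repair code that the same sentence offers as the derivation, and the rejected-report clause is impossible at record level too.

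On deaths, the defence is that a poorly documented cause is no ground for rejection when any cause counts, and that adjudication is the protocol's design. A wrongly rejected death is therefore a possibility that the rules permit, not something shown. But no prose removes that possibility, because SAP 2.2.2 repeats the requirement.

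A reader might infer that the reported hazard ratio rests on wrong statuses and dates. The documents do not support that. Nothing shows that the code was followed over the prose. Supplementary Table 2, in the post hoc analysis excluding peripheral arterial disease, has 661 of 677 and 687 of 695 participants at risk, so only 16 + 8 = 24 are outside the risk set, for reasons not given. That is indirect and says nothing about dates or deaths, but it gives no sign of large-scale dropping.

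A reader might also notice that the date line lists no flag for transient ischaemic attack. This has no shown effect: an accepted attack is dated through the hospitalisation or first-onset flag.

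**Conclusion.** The code is wrong as written. One clause can never apply, and the date line lacks the acceptance condition that the prose requires. For status and date, the defect is code that contradicts correct prose. For deaths, it is a rule in both places that does not match the all-cause endpoint.

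If the rules were run as written, randomised participants could be dropped, events misdated and deaths omitted. The effect on the hazard ratio is conditional. It is 0.006 or less with equal rejection by arm, and about 0.05 in either direction with 15% against 25%. These sizes rest on the assumed rejection rates, the assumed share of deaths, and dropping of participants without status. Unequal rejection is possible in an open-label trial, but the documents give no rejection counts, so no head count of affected participants can be given.

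**What to change.** Replace the code in SAP 4.1.1 with an event-level rule, and align SAP 2.2.2 with it:

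- Apply DECISION to each reported event separately.
- Set PEVENT=1 for any confirmed death from any cause, or any non-fatal event with DECISION=Yes.
- Set DATEPEVENT to the earliest date among those qualifying events only.
- Set PEVENT=0 for every other randomised participant, including those with only rejected events, censored as the prose already states.
- Use adjudication of confirmed deaths only to assign cause.

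The report should state which rule was run and give the number of rejected reports by arm, including any deaths. The cost is SAP wording and programming; no design feature or data collection changes. The treatment of deaths does narrow the committee's role, so the trial team should agree it explicitly.
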